## (2) Safety evaluation items

- ① The occurrence of inflammation, tumor formation, or death that cannot be ruled out as being related to the test device during the period of subcutaneous implantation of the test device
- ② Biocompatibility of the implanted biotube (inflammation, rejection, tumor formation, etc.)
- ③ Burst of implanted biotubes
- ④ Deaths related to implanted biotubes cannot be ruled out
- ⑤ Deaths within 12 weeks after implantation of biotubes
- ⑥ Other adverse events and malfunctions

[Rationale for setting]

Since the medical device is implanted in the body, it is necessary to carefully check whether it has any adverse effects on the body. In addition, the formed biotube is made of the patient's own tissue, but since the tissue formed subcutaneously will be used as blood vessels in another part of the body, it is

necessary to confirm that it can be safely implanted without any malfunctions and functions as a blood vessel.

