#### 4.4 Discontinuation criteria

- (1) When the principal investigator or co-investigator determines that it is difficult to continue the clinical trial due to the occurrence of adverse events or aggravation of the underlying disease.
- (2) When no biotube usable for bypass surgery, even fragmented ones, is formed at all, making it impossible to continue the clinical trial thereafter
- (3) If a subject withdraws consent to participate in the clinical trial
- (4) If it is discovered after enrollment that the subject does not meet the eligibility requirements
- (5) If it is discovered that the subject is pregnant after implantation of the investigational device but before implantation of the biotube
- (6) If a significant deviation from the clinical trial protocol is discovered
- (7) If bypass surgery is not required 24 weeks after BTM1 implantation, the entire BTM1 will be removed and the clinical trial will be discontinued, but the formation ability of the biotube will be evaluated.
- (8) Other cases in which the principal investigator or clinical investigator determines that the clinical trial should be discontinued

[Rationale for setting]

All of these were set from an ethical perspective and from the perspective of ensuring the safety of the subjects.

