#### 6.4.4 Implantation period of the test device and follow-up period

Implantation period of the test device: 4 to 24 weeks (in principle, 8 weeks or more)

Post-observation period: up to 12 weeks after implantation of the biotube

In addition, this period includes the pre-observation period from consent acquisition to registration (up to 8 days) and the follow-up period for adverse events (if adverse events that require follow-up occur).

[Rationale for setting]

The longer the implantation period, the more the tissue formation of the biotube progresses, but to avoid excessive worsening of the symptoms of lower limb ischemia, it is desirable to perform bypass surgery as soon as possible. Therefore, although it depends on the symptoms, the implantation period was set to about 2 months (8 weeks) in principle to ensure the formation of the biotube. In addition, since it was confirmed in non-clinical studies that the biotube could be formed after one month of implantation, it was considered acceptable to perform removal and bypass surgery even if the implantation period was between four and eight weeks if significant progression of ischemia was observed after implantation, and therefore the shortest implantation period was set at four weeks.

In addition, since symptoms usually improve around three months after implantation when bypass surgery is performed using an autologous vein, and since the results of non-clinical studies suggest that the implanted biotube is generally replaced by autologous tissue around three months after implantation, the observation period after implantation of the biotube was set at 12 weeks.

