Total length, length, presence or absence of tears or holes (if present, length), presence or absence of thickness/extremely thin parts (if present, length), presence or absence of uneven parts (if present, length), presence or absence of leakage, tensile strength, pressure resistance, presence or absence of preservation of samples for histopathological evaluation, usable length, presence or absence of preservation of biotubes, evaluation date, presence or absence of abnormalities in appearance (decomposition, decay, abnormal odor, discoloration, etc.), presence or absence of preservation of samples for bacterial testing

(19) Biotube transplantation

[Survey items]

Information on biotube transplantation

[Survey period]

Visit 7

[CRF contents]

Whether or not biotube transplantation was performed, transplant date, confirmation date of transplant postponement, transplant date of transplant postponement, graft used, combination method, graft (biotube number), length of biotube used, autologous vein (site, length), artificial blood vessel (product name, length), pressure resistance, reason for transplant discontinuation, whether or not biotube was connected, date of connection, length of biotube after connection, whether or not it was pressure resistant (if not, reason), whether or not biotube was repaired

(20) Concomitant medications and concomitant therapies

Concomitant medications and concomitant therapies refer to all medications used or all treatments and procedures performed after obtaining consent. However, implantation of a test device and biotube implantation are excluded.

[Survey items]

Target medications, treatments and procedures

[Survey period]

From confirmation of eligibility to Visit 13 or discontinuation.

[CRF content]

Presence or absence of concomitant medications (if there are concomitant medications, the name of the drug (brand name or generic name), route of administration, single dose, frequency of administration, duration of administration, reason for administration), presence or absence of concomitant therapy (if there are

concomitant therapies, the name of the therapy, start date, end date, purpose of treatment)

(21) Adverse events

[Survey items]

Whether or not an adverse event occurred, and if so, information related to the adverse event

[Survey period]

From implantation of the study device until Visit 13 or discontinuation.

[CRF content]

See "7. Safety evaluation"

(22) Malfunctions

[Investigation items]

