## 7.2 Adverse Events

### 7.2.1 Definition of Adverse Events

Adverse events are any undesirable or unintended disease or disorder or its symptoms (including abnormalities in clinical test results) that occur in subjects treated with the investigational device, regardless of whether they are causally related to the investigational device. Adverse events will be collected from the time of treatment with

the investigational device until the end of the observation period or discontinuation of each subject (excluding the follow-up period), and the severity will be determined according to the National Cancer Institute Common Terminology Criteria for Adverse Events (NCI CTCAE v5.0). If there is no applicable item, the grade will be determined with reference to Table 7.1.

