### (2) Procedural success of bypass surgery including peripheral anastomosis using a biotube formed by the test device

It will be visually evaluated whether the biotube can be sutured without damage or cutting using the same technique as a bypass surgery using a normal vein. It will be visually evaluated whether bleeding from the anastomosis site can be controlled, and there is no blood leakage, tearing, or swelling from the biotube wall. After releasing the vascular clamp, pulsatile blood flow is confirmed and the flow rate is measured with a flowmeter to evaluate peripheral revascularization. Note that "technical success" in this evaluation item refers to cases where bypass surgery was performed using only the biotube as a bypass graft (including cases where fragments of the biotube were joined together), and does not include cases where bypass surgery was performed by joining an autologous vein or an artificial blood vessel.

(3) Patency of the biotube at 12 weeks after implantation

During the follow-up period, blood flow in the biotube is evaluated by lower limb arterial echocardiography. If possible, the shape of the biotube is observed by lower limb CT angiography or lower limb arteriography to evaluate the presence or absence of abnormalities such as stenosis or swelling.

(4) Improvement of symptoms (improvement of ischemic pain, improvement of wounds)

The pain improvement rate, wound improvement rate, wound area reduction rate, and granulation formation rate are evaluated at the time of eligibility confirmation, at the time of biotube implantation, and 1, 4, 8, and 12 weeks after biotube implantation. In addition, the Wiffl score is also evaluated at the time of eligibility confirmation, and 1, 4, 8, and 12 weeks after biotube implantation.

(5) Avoidance of major amputation

The avoidance rate of major amputation of the target lower limb during the follow-up period will be examined.

(6) Implementation rate of additional treatment during implantation of the study device and after biotube implantation

The rate of revascularization other than bypass surgery using the biotube will be evaluated from implantation of the study device to the end of the follow-up period.

(7) QOL during implantation of the study device and after implantation of the biotube

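### Outcome collection stops at discontinuation, so 12-week death and limb status can go unascertained in a grafted subject who is discontinued early

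*Protocol*

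**What the plan says.** **What is to be reported.** Safety item 5 in 3.2(2), repeated in 9.3(5), is "Deaths within 12 weeks after implantation of biotubes". For limb loss, 8.2(5) states: "The avoidance rate of major amputation of the target lower limb during the follow-up period will be examined". Section 6.4.4 gives the length of observation after grafting: "Post-observation period: up to 12 weeks after implantation of the biotube".

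**When collection ends.** Adverse events are surveyed "From implantation of the study device until Visit 13 or discontinuation" (6.5.1(21)), and 7.2.1 sets the same end point, leaving out the follow-up period. Concomitant medications and procedures are recorded "From confirmation of eligibility to Visit 13 or discontinuation" (6.5.1(20)). Malfunctions, expressly including those of the biotube, stop at Visit 13 or cancellation (6.5.1(22)).

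**Who can be discontinued.** Criterion 4.4(1) covers cases where it is "difficult to continue the clinical trial due to the occurrence of adverse events or aggravation of the underlying disease". Other criteria that can apply after grafting are late-found ineligibility, a significant deviation and investigator judgment. Table 6.5 has a discontinuation column for the post-observation period, so discontinuation after grafting is foreseen.

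**What happens afterwards.** Section 6.5.2 asks for the examinations in the discontinuation column. If an adverse event requires it, the subject is also followed, in principle, to recovery or improvement. Section 7.4(3) asks for continued monitoring of an event and confirmation of its outcome. Section 7.2.7 lists death among the outcomes, but lets the investigator end follow-up judged unnecessary if the reason is written down.

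**The concern.** Safety item 5 has a fixed window counted from transplantation. The records that would fill it have a window that closes at discontinuation. The two coincide only for subjects who reach Visit 13.

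For a grafted subject discontinued earlier, nothing in the protocol requires anyone to find out whether that subject was alive, or still had the limb, at 12 weeks. This is a gap in collection and not in analysis: neither a statistical analysis plan nor the case review meeting can recover a status that nobody recorded.

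What is at stake is how the 12-week mortality and limb-loss figures read in a first-in-human, uncontrolled trial of 12 subjects. An unknown that is tallied as no event lowers the reported rate. Since deterioration is one of the reasons for discontinuation, the unknowns need not be a random subset.

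**Working it through.** **Step 1. Plan's own figure.** The target of 12 cases (9.5) rests on device sizes, implantation sites, feasibility and the interim analysis. No event rate, alpha, power or discontinuation rate lies behind it, so there is nothing to reproduce, and the target itself is not disputed here.

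**Step 2. What is captured after a post-graft discontinuation.**

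| Situation | Route in the protocol | 12-week death and limb status |
|---|---|---|
| Discontinued with an open adverse event, which later leads to death or limb loss | 6.5.2, 7.4(3), 7.2.7 | Probably captured, unless follow-up is ended early under 7.2.7 |
| Discontinued with an open event; a new, separate event follows | None: 6.5.1(21) and 7.2.1 have closed | Not secured |
| Discontinued for ineligibility, deviation or investigator judgment, with no open event | Examinations at the time of discontinuation only | Not secured |
| Reintervention or rupture arising after discontinuation | None: 6.5.1(20) and (22) have closed | Not secured, except as the outcome of an open event |

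**Step 3. Size, for illustration.** Inputs: n = 12 (9.5), assuming that all 12 are grafted. The number d discontinued before week 12 with unknown later status is also an assumption. With no recorded deaths, the true proportion lies between 0/n and d/n.

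Exact (Clopper-Pearson) 95% limits:
- 0/12: upper limit = 1 - 0.025^(1/12) = 26.5%
- 1/12 = 8.3%: 0.2% to 38.5%
- 2/12 = 16.7%: upper limit 48.4%
- 3/12 = 25.0%: upper limit 57.2%

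So d = 1 leaves 0% to 8.3%, d = 2 leaves 0% to 16.7%, and d = 3 leaves 0% to 25.0%. The same bounds apply to major amputation. If fewer than 12 are grafted, each unknown moves the proportion by 1/n, which is more than 8.3 points.

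**Step 4. Chance that at least one event is missed.** With an assumed event risk q per discontinued subject over the unobserved time, the chance is 1 - (1 - q)^d:

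| d | q = 10% | q = 25% | q = 50% |
|---|---|---|---|
| 1 | 10% | 25% | 50% |
| 2 | 19% | 44% | 75% |
| 3 | 27% | 58% | 88% |

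Neither d nor q is given in the documents. The table shows only that one or two such subjects are enough to matter at this sample size.

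**The case against.** The strongest reply is that the most worrying route is also the best covered. A subject discontinued under 4.4(1) will usually have an open adverse event. Sections 6.5.2 and 7.4(3) then follow that event to its outcome, 7.2.7 lists death as an outcome, and 3.3 places such follow-up outside the participation period, so it can run on. This stands, and it limits the finding.

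Four stronger readings are therefore tempting but not supported:

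- A reader might infer that every death or limb loss after discontinuation is lost. Take a graft that occludes, a discontinuation at week 3 for worsening ischemia, and death at week 8. The ischemia is an open adverse event, so its outcome would probably be captured at least in part, and the occlusion was already on record.
- A reader might take amputation to be a fixed 12-week endpoint. Section 8.2(5) names only the follow-up period. For a discontinued subject the end of that period is unclear, which is a reason to define it, but the fixed window belongs to the death item alone.
- A reader might infer that discontinued subjects drop out of the analysis. Section 9.1 does not remove them from the FAS or the safety set; their handling goes to the case review committee. The defect is an unknown outcome. Counting it as no event is a risk and not a stated rule.
- A reader might conclude that the loss is mainly among those at highest risk. That is partly an inference from 4.4(1). For ineligibility or deviation, the documents show no link with prognosis.

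It can also be said that safety item 5 is listed apart from other adverse events and so carries its own 12-week window. That is a fair reading of the definition, but no survey item in 6.5.1 collects vital status to match it. The committee review one month after transplantation (3.4) does not fill the gap either, since it falls well before week 12.

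**Conclusion.** The concern holds in a limited form. The collection rules close at discontinuation, one named safety item needs 12 weeks from transplantation, and nothing secures vital or limb status at 12 weeks for a grafted subject who is discontinued early without an open event or who has a new event afterwards. Part of that loss may be informative, because worsening disease can lead to discontinuation.

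If all 12 subjects are grafted, each unknown widens the possible death or amputation proportion by 8.3 percentage points. How often this would happen cannot be judged from the documents.

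Severity is moderate, not a condition for proceeding. The trial is exploratory and sets no threshold for death or amputation. Its primary endpoint is settled by whether bypass can be done with the biotube alone (8.1), which later discontinuation does not change.

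**What to change.** In 6.5.2, 6.5.1(20)-(22) and 7.2.1, separate stopping trial procedures from ascertaining outcomes. For every subject who received a biotube, unless consent to follow-up is withdrawn, record the following to 12 weeks after transplantation, from the hospital record or a telephone contact:

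- vital status, with date of death
- major amputation of the target limb
- revascularization of the target limb
- rupture of the biotube

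State in 3.2(2), 8.2(5) and 9.3 that safety item 5 and major amputation use this window for all grafted subjects, whether or not discontinued. The change concerns data collection only and alters no rule on treatment or on who is discontinued.

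The cost is a wording amendment and one check per discontinued grafted subject. The reported event rates may look slightly less favourable. Subjects who withdraw consent to follow-up will remain unknown.

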6.5.2 Examinations and observations after cancellation

If the study is discontinued for any reason after registration, it will be treated as a discontinued case. If the study is discontinued after implantation of the test device, the examinations and observations listed in "6.5 Observation and Examination Schedule" and "6.5.1 Observation, Investigation, and Examination Details" will be carried out. In addition, if follow-up is required due to an adverse event, the patient will be followed up until recovery or improvement in principle.

7. Safety assessment

7.1 Clinical test values

The investigator or subinvestigator will compare the test values and measurements taken after implantation of the investigational device with the results of tests taken after obtaining consent, and determine whether there are any abnormal changes. When determining whether there are any abnormal changes in clinical test values, the National Cancer Institute Common Terminology Criteria for Adverse Events (NCI CTCAE v5.0) should be used as a reference, and if there is no corresponding item, the Grade (severity) should be evaluated with reference to Table 7.1.

If abnormalities in clinical test values are observed, the investigator or subinvestigator will determine whether the abnormality should be treated as an adverse event with reference to the following items.

- (1) When clinical trial treatment is discontinued due to abnormal laboratory test values
- (2) When drug or surgical intervention is performed to improve abnormal laboratory test values
- (3) When a correlation with clinical symptoms is found
- (4) When a correlation with a serious adverse event is found
- (5) When the principal investigator or co-investigator determines that an adverse event should be treated as such, other than the above (1) to (4)

Table 7.1 Grade Classification (Severity) Criteria for Adverse Events

| Grade | severity                                                                                                                                                              |
|-------|-----------------------------------------------------------------------------------------------------------------------------------------------------------------------|
| 1     | Mild. Asymptomatic or mild symptoms. Clinical or laboratory findings only. No treatment required.                                                                     |
| 2     | Moderate. Minimal/local/non-invasive treatment required. Age-appropriate limitation in ADL other than self-care.                                                      |
| 3     | Severe or medically significant, but not immediately life-threatening. Hospitalization or prolonged hospitalization required. Disabling. Limitation in self-care ADL. |
| 4     | Life-threatening. Urgent intervention required.                                                                                                                       |
| 5     | Death due to adverse event (AE).                                                                                                                                      |

## 7.2 Adverse Events

### 7.2.1 Definition of Adverse Events

Adverse events are any undesirable or unintended disease or disorder or its symptoms (including abnormalities in clinical test results) that occur in subjects treated with the investigational device, regardless of whether they are causally related to the investigational device. Adverse events will be collected from the time of treatment with

the investigational device until the end of the observation period or discontinuation of each subject (excluding the follow-up period), and the severity will be determined according to the National Cancer Institute Common Terminology Criteria for Adverse Events (NCI CTCAE v5.0). If there is no applicable item, the grade will be determined with reference to Table 7.1.

#### 7.2.2 Description of adverse events

In principle, the name of the adverse event is recorded in the case report form as the diagnosis or disease name. If the diagnosis or disease name cannot be specified or if the investigator or co-investigator determines that it is appropriate not to use the diagnosis or disease name, the clinical symptoms or signs (including abnormal laboratory test values) are recorded as the adverse event name in the case report form.

For all adverse events that occurred, the investigator or co-investigator should record the name of the adverse event, the date of onset, the date of outcome, the severity, seriousness, the reason for determining that the adverse event was serious (see 7.2.3 Serious Adverse Events (1) to (7)), the causal relationship with the investigational device, the causal relationship with the biotube, the outcome (recovered, remitted, with aftereffects, not recovered, death), the treatment taken for the investigational device, the treatment taken for the biotube, the treatment taken to treat the adverse event, and any comments in the adverse event section of the case report form.

#### 7.2.3 Serious adverse events

Adverse events that fall under any of the following categories will be treated as serious adverse events.

- (1) Death
- (2) Potential for death
- (3) Permanent or significant disability or dysfunction
- (4) Potential for disability
- (5) Requires hospitalization or extended hospitalization for treatment
- (6) Causes congenital abnormality
- (7) Other serious medical conditions

However, hospitalizations for the sole purpose of carrying out treatment or examinations that were planned before participation in the clinical trial (before consent was obtained) during the clinical trial (scheduled surgery, examinations, etc.), hospitalizations for purposes other than treatment or examinations associated with an

adverse event (health checkups, etc.), and no undesirable medical events will be treated as serious adverse events.

